### Study objectives

This study protocol aims to design, implement and evaluate a transferable cost-effective program for lifestyle management of obesity in infertile women integrated into the fertility clinics. To achieve this goal, the proposed project will focus on four specific objectives:To design and implement an interdisciplinary program for lifestyle management of obese women, or overweight women with PCOS, who seek fertility treatment at the CHUS, a fertility clinic with provincial coverage of fertility treatments and satellite access to *in vitro* fertilization (IVF);To evaluate lifestyle benefits of this program and assess its impact on fertility, pregnancy complications and neonatal outcomes, as compared to a randomly assigned control group and to similar women seen in three fertility clinics across Canada with and without public coverage of fertility treatments;To assess cost per live birth, and other measures of cost-effectiveness, of this program compared to the control group and three fertility clinics across Canada with and without public coverage of fertility treatments; andTo effectively transfer knowledge obtained through these activities to relevant stakeholders in the health care and public health sectors, including policy-makers, decision-makers, health care professionals and patients.

## Methods/Design

### Study design and setting

The proposed study relies on a participatory research approach which will combine quantitative and qualitative assessments. The impacts of the lifestyle program that will be developed will be assessed using a randomized controlled trial in one academic center. The study was registered to ClinicalTrials.gov (NCT01483612).

The RCT will be conducted at the CHUS fertility clinic, a fertility clinic with satellite access to IVF. The clinic offers care to patients with a range of reproductive problems including infertility, recurrent pregnancy loss, anovulation, PCOS, hyperprolactinemia, endometriosis, etc. The clinic has a successful ovulation induction and superovulation program including intrauterine insemination and access to donor sperm. Since 2011, it offers an IVF program in collaboration with Procrea Cliniques initially, and subsequently with the assisted reproduction center of the CHU Ste-Justine, where only the egg retrievals and embryo transfers are performed (evaluation of patients, protocol prescription, monitoring and decision making before and during cycles is done in Sherbrooke). Clinical outcomes and costs will be compared to a randomly assigned control group and to similar women seen in three fertility clinics across Canada not offering specific weight loss interdisciplinary lifestyle program: 1) an intra-provincial clinic (Procrea Cliniques, Montreal) with public coverage of fertility treatments; 2) 2 extra-provincial clinics (Centre for Fertility and Reproductive Health and IVF Unit at Mount Sinai Hospital, Toronto; and Fertility Clinic of Royal Alexandra Hospital, Edmonton) without public coverage of fertility treatments. These centers offer the full range of ART on site.

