**Discussion:**

This study will generate new knowledge about the implementation, impacts and costs of a lifestyle management program in obese infertile women. This information will be relevant for decision-makers and health care professionals, and should be generalizable to North American fertility clinics.

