### Data analyses and interpretation

For objectives 1–2, all comparisons between randomized groups at the CHUS will follow both the intent-to-treat and/or per-protocol principles, and will consider results at the end of study. For repeated measures, the last-observation-carried-forward method will be used for women who drop out or become pregnant (depending on analyses). Time-to-event analyses will also be performed for fertility outcomes, with censoring for drop out alone, as well as for anthropometric outcomes, with censoring for both drop out and occurrence of pregnancy. Univariate analyses will compare the change in a variable in the intervention group with the change in this variable in the control group, using two-tailed unpaired *t* tests (for continuous variables) and chi-square or Fisher’s exact tests (for categorical variables). Changes in weight will also be compared for the same follow-up duration with changes for women seen at the other fertility clinics, using ANOVA tests. For the other variables, only end-of-study comparisons will be performed between the two groups in Sherbrooke and the three other fertility clinics, using ANOVA tests (for continuous variables) and logistic regressions (for categorical variables). Bonferroni-corrected p-values will be performed to adjust for the multiplicity of comparisons and an α level of 5 % will be considered significant for all analyses. Continuous variables that are not normally distributed will be log-transformed in order to ascertain normal distribution. Multivariate analyses will also be used in order to adjust for baseline differences and for potential confounders, and to determine independent predictors of outcomes. Triangulation will be performed between quantitative and qualitative data.

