### Sample size

Our sample size estimation is based upon our primary outcome (see Objective 2), which is live-birth rates between randomized groups at the CHUS. Based on the Fertility Fitness Program, the inclusion of 58 women per group will provide our study a power of 80 % to identify a doubling in live-birth rates with our program (25 to 50 %, α = 5 %). Assuming a dropout rate of 10 % (these women are usually highly motivated), our final estimated sample size will be 128 women. For other objectives and outcomes, it would be difficult to assess power because similar evaluations have not been previously reported.

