## Discussion

This paper has outlined the protocol of a study assessing clinical outcomes and costs of a transferable interdisciplinary lifestyle intervention, before and during pregnancy, in obese infertile women. We are using a RCT design for proximal clinical outcomes, and mixed design for cost-effectiveness evaluation and qualitative assessment for the purpose of future dissemination and knowledge transfer. To our knowledge, we are the first in the world to conduct such a program with lifestyle intervention continuing throughout fertility treatments and pregnancy. This project is very important as it will generate new knowledge about the implementation, impacts and costs of a lifestyle management program in obese infertile women. The results of this study will provide valuable information on feasibility and transferability of such a program, including identification of barriers and solutions. We expect that our program will improve the lifestyle and fertility of the participants and reduce maternal and fetal complications during pregnancy, as compared with our different control groups. A significant reduction in cost per live birth and cost-effectiveness ratio is also anticipated.

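### The programme runs only at the CHUS, so contrasts with the three outside clinics mix programme effect with clinic difference and should be descriptive, with programme conclusions resting on the randomised arms

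*Protocol article*

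**What the plan says.** Under Study objectives, Objective 2 (clinical impact) and Objective 3 (cost-effectiveness) each name two kinds of comparator: the randomised control group and similar women at three other Canadian clinics. Study design and setting repeats this: outcomes and costs will be compared "to similar women seen in three fertility clinics across Canada not offering specific weight loss interdisciplinary lifestyle program". One of these clinics is in Quebec with public coverage; the other two are in other provinces without it. Of all three the section says "These centers offer the full range of ART on site", whereas the CHUS has satellite access to IVF.

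Data analyses and interpretation sets end-of-study comparisons "between the two groups in Sherbrooke and the three other fertility clinics, using ANOVA tests (for continuous variables) and logistic regressions" for categorical variables, with Bonferroni-corrected p-values and multivariate adjustment for potential confounders, and states that "an α level of 5 % will be considered significant for all analyses". Weight change is also compared across clinics by ANOVA. No clinic-level variance term is mentioned.

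The main Discussion expects lifestyle, fertility and pregnancy benefits "as compared with our different control groups". Its limitations paragraph acknowledges that the programme runs in a single clinic, and answers the coverage limitation by pointing to the comparison with clinics where treatment is not covered. The Abstract says the information "should be generalizable to North American fertility clinics".

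**The concern.** A comparison listed under the programme's impact objectives, tested at 5 % and described as a comparison with control groups will be read as evidence about the programme. Against an outside clinic it is evidence about the programme plus everything else that distinguishes the CHUS from that clinic. Women are the unit of analysis, but the programme was assigned to one clinic out of four, so the standard error omits the variation that matters for that reading.

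Two conclusions are at stake. First, a significant difference from an outside clinic could be reported as supporting effectiveness or lower cost per live birth when it reflects an ordinary difference between clinics. Second, data from uncovered clinics could be cited as showing that the effect carries over to such settings, although no woman there receives the programme. Decision-makers are the stated audience for both.

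**Working it through.** **The plan's own figure.** Sample size states that "the inclusion of 58 women per group will provide our study a power of 80 % to identify a doubling in live-birth rates" (25 to 50 %, α = 5 %). Taking a two-sided test with pooled variance and p̄ = 0.375:

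n = [1.96·√(2·0.375·0.625) + 0.842·√(0.25·0.75 + 0.50·0.50)]² / 0.25² = 57.7, so 58 per group.

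The figure reproduces. Adding 10 % gives 116 × 1.10 = 127.6, so 128 in total, or 64 per arm under 1:1 allocation. This calculation concerns the randomised comparison within the CHUS only.

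**What each contrast estimates.** Let τ be the programme effect, and let c₀ and cⱼ be the underlying levels at the CHUS and at outside clinic j.

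- Programme arm − CHUS control = τ
- Programme arm − clinic j = τ + (c₀ − cⱼ)
- CHUS control − clinic j = c₀ − cⱼ

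Subtracting the third line from the second returns the first: the outside clinic cancels. It therefore adds no information on τ beyond the randomised contrast. It informs only on c₀ − cⱼ, that is, on how typical the CHUS is.

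**What differs by clinic**, from Study design and setting and the Discussion:

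| Feature | CHUS vs Quebec clinic | CHUS vs each extra-provincial clinic |
|---|---|---|
| Programme | differs | differs |
| Satellite vs on-site ART | differs | differs |
| Province | same | differs |
| Public coverage | same | differs |

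These are clinic-level features, constant within a clinic. Covariates measured on women cannot remove them. A random clinic effect does not rescue the contrast either, since only one clinic has the programme.

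**Size of the excess rejection.** Inputs:

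- α = 5 % (Data analyses and interpretation).
- Two-sided testing. The protocol states this only for its "two-tailed unpaired" t tests; it is assumed here.
- m = 64 women per group. The 64 follows from 128 for the programme arm; the chart count per outside clinic is not given and is set equal by assumption.
- Residual between-clinic ICC of 0.005 to 0.05. This is not given and is an assumption.
- No programme effect.

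For two clinic means of m women each, the true variance of the difference is the patient-level variance times

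DE = 1 + (m − 1)·ICC.

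The true rejection rate is 2·[1 − Φ(z / √DE)], where z = 1.960 for one uncorrected test, 2.394 for Bonferroni over 3 pairs (α = 0.0167), and 2.807 over all 10 pairs of five groups (α = 0.005). Around a 25 % live-birth rate the between-clinic SD is √(ICC·0.25·0.75).

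| ICC | SD, points | DE | √DE | Uncorrected (nominal 5 %) | Over 3 pairs (nominal 1.7 %) | Over 10 pairs (nominal 0.5 %) |
|---|---|---|---|---|---|---|
| 0.005 | 3 | 1.315 | 1.15 | 8.7 % | 3.7 % | 1.4 % |
| 0.01 | 4 | 1.63 | 1.28 | 12.5 % | 6.1 % | 2.8 % |
| 0.02 | 6 | 2.26 | 1.50 | 19.2 % | 11 % | 6.2 % |
| 0.05 | 10 | 4.15 | 2.04 | 33.6 % | 24 % | 17 % |

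With 100 women per group the uncorrected column becomes 10.9 / 16.5 / 25.6 / 42.2 %.

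**Sensitivity.** A simulation of the programme arm against the three clinics pooled, with 50 to 200 charts each and the ICC set on the logit scale, gives lower uncorrected rates for a binary outcome: 7–8 % at ICC 0.005, 9–11 % at 0.01, 14–16 % at 0.02 and 25–29 % at 0.05. At ICC 0 it returns 5 %. The randomised contrast within the CHUS stays at 5 % for every ICC.

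**The case against.** Several points on the other side are sound.

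- **The design already contains the remedy.** The five-group layout includes the CHUS control arm, so the programme effect is identified within the CHUS and the clinic difference is visible from the control arm. A reader might infer that the trial cannot separate programme from clinic at all. It can; only the direct programme-versus-outside contrasts cannot.
- **The Quebec clinic shares province and coverage with the CHUS.** A reader might infer that all three comparisons are confounded with both. That holds only for the two extra-provincial clinics.
- **Bonferroni correction is planned.** A reader might infer that false positives run well above 5 % in every case. The documents do not support that, because they give neither an ICC nor chart counts. At the low end of the assumed range the rate per contrast over 10 pairs is 1.4 %. Yet Bonferroni deals with the number of tests, not with an omitted variance: 1.4 % is still nearly three times the 0.5 % that the corrected test promises.
- **The tests have their nominal size for a narrower null**, namely that these particular groups have equal means. This is correct. The excess arises only when rejection is read as a programme effect. The analysis section does not itself say that, but the objectives and the Discussion invite that reading.
- **The Discussion concedes a good deal**: a single clinic, retrospective data, the coverage difference, and the outside comparison as a first step towards a multicentre trial. It does not concede that programme and clinic are inseparable in these contrasts, and its reply on coverage relies on clinics where the programme is absent.

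**Conclusion.** The concern holds in limited form. Contrasts of the programme arm with outside clinics, for clinical outcomes and for cost, estimate programme effect plus clinic difference. None of the stated analysis tools removes the second term. Read as tests of the programme, they reject too often whenever clinics differ: under the assumptions above, about 9 to 34 % instead of 5 % uncorrected, 4 to 24 % instead of 1.7 % over 3 pairs, and 1 to 17 % instead of 0.5 % over 10 pairs. These figures illustrate the size; they are not properties of the plan, because the ICC and the chart numbers are assumed.

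The generalisability argument has a separate weakness that depends on no ICC: clinics where no one receives the programme cannot show its effect without public coverage.

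A reader might infer that the trial's main result is at risk. It is not. The primary live-birth comparison and its sample size rest on randomised groups within one clinic.

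**What to change.** - **Study objectives, the Objective 2 and 3 evaluation sections, Data analyses and interpretation, and Discussion:** state that all conclusions on programme effect and cost-effectiveness rest on the randomised CHUS arms. The objectives must change along with the analysis text, or the two will disagree.
- **Outside clinics:** label the comparison descriptive. Give estimates and intervals by clinic, with CHUS control versus each clinic as the benchmark, and state that the intervals exclude between-clinic variation.
- **Abstract and Discussion:** do not use the outside clinics as evidence that the effect generalises to clinics without public coverage. Leave that question to the multicentre trial that the Discussion foresees.

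No new data are needed. The cost is the loss of p-values for programme versus outside clinics and of the broad generalisability statement, plus a restatement of two objectives.

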### Study participants

Study participants will be recruited among all women consulting at the CHUS fertility clinic. The staff will assist the research team in identifying potential participants. To be included in the study, women must fulfill the following inclusion criteria: 1) infertility; 2) aged between 18 and 40 years; and 3) obesity (BMI ≥30 kg/m^2^) or overweight if PCOS (BMI ≥27 kg/m^2^). Women will be excluded if they had bariatric surgery or plan for it and/or if natural conception is impossible or highly unlikely (tubal factor, severe male factor infertility, etc.). Infertility will be defined as: 1) failure to achieve a clinical pregnancy after 12 months or more of regular unprotected sexual intercourse in women who are under 35 years with regular menstrual cycles; 2) women who do not have regular menstrual cycles, or are older than 35 years and have not conceived during a 6-month trial period; or 3) women with a known cause of infertility. Eligible patients will be referred to the research coordinator to obtain their individual informed consent prior to baseline data collection.

### Ethical considerations

The proposed research was reviewed and approved by the Institutional Research Ethics Review Boards of the CHUS and other fertility clinics. Both research participants and health professionals will be duly informed and consent will be obtained in writing prior to evaluations or focus groups. This includes the 20 patients who will be randomly selected from other Canadian fertility clinics to be evaluated at the end of the study using the same questionnaires and focus group as patients at the CHUS. The main ethical consideration of the proposed research is confidentiality issues that will be minimized. All data will be coded, archived for at least 5 years and then destroyed.

### Randomisation

An independent statistician will use computerised random number generation to allocate each participant to the intervention or control group. Randomisation will be stratified according to the PCOS or non-PCOS status, based on clinical diagnosis in the patient’s record. Sequences will be generated using permuted block randomisation, with block sizes of two, four or six entries. The allocation sequence will be concealed in corresponding sequentially numbered opaque envelopes. After a participant has completed baseline assessments, the research coordinator will open the envelope to reveal the group allocation to the participant. Participants will be informed of their group assignment at that time.

### Intervention

#### Control arm

Participants assigned to the control group will receive standard fertility treatments, which will be initiated as soon as clinically indicated. Standard fertility treatments may include lifestyle counselling by the obstetrician-gynecologist certified in gynecologic reproductive endocrinology and infertility (GREI), reproductive endocrinologist or fertility specialist in charge of the care of the patient.

#### Intervention arm

Participants allocated to the intervention group will be invited to participate in the interdisciplinary lifestyle intervention and will have to delay other fertility treatments for six months. After 6 months of lifestyle intervention alone, women who are not pregnant will begin pharmacologic fertility treatments, as indicated, in conjunction with the lifestyle intervention that will continue to be offered. The aim of the intervention will be to implement progressive and sustainable lifestyle changes in order to reach a modest weight loss. Women will be invited to individually meet with a dietitian and a kinesiologist (20–30 min each) at 0, 3, 6 weeks and then every 6 weeks over a period of 18 months or until the end of pregnancy. A follow-up phone call/email will also take place once between each meeting for additional support. The dietitian will use 3-day food records to evaluate the women’s food intake throughout the program. To help improve patient’s diet, Canada’s Food Guide and the “Healthy Plate” [51] will be the main tools use for nutritional counselling. The kinesiologist will be responsible for taking anthropometric measures and vital signs and for coaching women to increase their physical activity level. A pedometer will be offered to assist the patient. Patients will be guided by the dietitian and the kinesiologist to formulate S.M.A.R.T goals (specific, measurable, attainable, realistic, and timely) at each meeting. The members of our interdisciplinary team will be trained in motivational interviewing. This training can positively affect the attitude to behaviour change in obese infertile women [52].

Besides individual intervention, women will benefit from a series of 12 educational group sessions (45-minute interactive small group workshops and 45-minute physical activity) covering various topics relevant to obesity management and fertility (Table 1). The workshops will be conducted by either the dietitian or psychologist and the demonstration of physical activity will be performed by the kinesiologist. These group sessions will take place weekly. When a pregnancy is confirmed, the woman will be met to set new objectives specific to her pregnancy, including an optimal gestational weight gain based on Institute of Medicine guidelines [53]. Partners will be invited to join individual meetings and strongly encouraged to assist all group sessions. To our knowledge, this is the first study assessing a lifestyle intervention in obese infertile women that is continued during fertility treatments and pregnancy.

**Table 1 Tab1:** Topics of the interactive workshops and physical activities of the Obesity-Fertility group sessions program

Sessions	Interactive workshops	Physical activities
1	*Nutrition:* Canada’s Food Guide	Walking
2	*Psychology:* Couple Communication	Aquafitness
3	*Nutrition:* Energy Density of Foods: Healthy Substitutions for Weight Loss	Step Aerobics
4	*Psychology:* Stages of Behaviour Change and Motivation	Strength Training at Home
5	*Nutrition:* Environmental Factors – Impact on Food Intake	Interval Walking
6	*Psychology:* Sleep and Relaxation	Yoga
7	*Nutrition:* Managing Hunger and Satiety	Exercising While Watching TV
8	*Psychology:* Eating Disorders vs. Compulsive Overeating and Actions Strategies	Aquafitness
9	*Nutrition:* Meal Planning Tips/ Alcohol and Smoking	Walking in Combination with Cardio and Muscular Endurance Exercises
10	*Psychology:* Self-Esteem and Body Image	Strength Training with Exercise Ball and Resistance Band
11	*Nutrition:* Understanding a Food Label	Circuit Training
12	*Psychology:* Behaviour Self-Assessment	Aerobic Dance Workout

### Committees overseeing the study

To facilitate the inclusion of all relevant stakeholders, four committees will be involved throughout program development and implementation, as well as the evaluation process.

#### Steering committee

This committee will bring together relevant medical experts of various disciplines (endocrinology, obesity, GREI) and health care decision-makers from the CHUS. It will be responsible for supervising the development of the intervention, the planning of the evaluation, and the monitoring of the intervention implementation at the CHUS. It will overlook the work of all subcommittees and the course of implementation, with difficulties and proposed solutions, and will decide the directions for the intervention and the research plan. Steering committee meetings will occur regularly, as needed, and will also serve as knowledge transfer activities where decision-makers and knowledge users will be informed about the implementation and the results of the research.

